#### MEP and hemispheric excitability conversion degree

The MEP amplitudes of patients and controls will be analyzed by nonparametric tests. The MEP latency and central motor conduction time (CMCT) are analyzed with independent samples *t* tests. The hemispheric excitability conversion degree [ln(DH/NDH ratio)] [13] is compared with generalized estimating equations (GEEs) [27] with respect to disease course (1 m, 2 m, 4 m, 6 m, and 12 m). **P* < 0.05 was regarded as a significant difference.

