**Methods:**

This study is a 12-month prospective cohort study. The neurophysiological and overall functional status of the participants will be assessed. The primary outcomes included single-pulse and paired-pulse TMS. The second outcome included functional near-infrared spectroscopy (fNIRS) measurements. Overall functional status included total motor score, modified Ashworth scale score, ASIA Impairment Scale grade, spinal cord independence measure and modified Barthel index. The data will be recorded for individuals with SCI at disease durations of 1 month, 2 months, 4 months, 6 months and 12 months. The matched healthy controls will be measured during the same period of time after recruitment.

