### Participants

#### Inclusion and exclusion criteria

The inclusion criteria for individuals with SCI were as follows: (a) 18–75 years old, right-hand dominant (Edinburgh Handedness Inventory); (b) diagnosed with SCI [15]; (c) stable MEP in the M1 hand area was detectable; (d) no cognitive impairment (Mini-Mental State Examination score ≥ 24) [16]; (e) disease course ≤ 1 month (from SCI onset to first assessment); and (f) agreed to participate in this study and signed the informed consent form. Exclusion criteria: (a) serious nervous system disease, unable to tolerate relevant tests; (b) upper limb fracture, arteriovenous fistula or other diseases leading to movement disorder; (c) ferromagnetic implants in the head or neck; (d) implantation of a cardiac pacemaker; (e) severe coagulation disorder, severe cardiac insufficiency or uncontrollable hypertension: systolic blood pressure > 160 mmHg or diastolic blood pressure > 100 mmHg; (f) other serious systemic diseases such as tumors; (g) taking drugs that may affect the TMS examination within a week, including baclofen, diazepam and other drugs [17]; (h) absolute contraindications for TMS examination.

The inclusion criteria for healthy controls were as follows: (a) 18–75 years old, right-hand dominant (Edinburgh Handedness Inventory); and (b) stable MEPs. Exclusion criteria included the above situations in which TMS could not be performed.

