#### Recruitment and sample selection

Potential participants will first be screened by nurses based on inclusion and exclusion criteria and informed about the study during a consultation with nurses if they meet the inclusion criteria. To assess the external validity of the recruited sample of participants, age and gender will be collected for those participants who refuse to participate in the study [18]. If potential participants are interested in participating in this study, their names will be placed on a trial list. The investigator will contact the participants and explain the procedure. If the participants agree, an informed consent form will be sent. If the participants have any questions, they can contact the investigator.

Upon receipt of the signed informed consent form, the participants will be registered in the electronic case report form (eCRF), and the basic information will be recorded at baseline. Then, the doctor will assess the neuroelectrophysiology data, and the ability to perform ADLs and motor function will be evaluated by an occupational therapist. The participants received a reminder or were contacted by phone at subsequent testing time points. Measurements are recorded by the nurse specialist in the Electronic Patient Record.

After recruitment, individuals with SCI will be measured at disease durations of 1 month, 2 months, 4 months, 6 months and 12 months, including single pulse TMS (spTMS) to evaluate the CSE in bilateral M1 hand areas, ppTMS to evaluate the intracortical excitability in bilateral M1 hand areas, and fNIRS to evaluate bilateral M1 hand area blood flow. All subjects will receive an assessment scale. The matched healthy controls will be measured during the same period after recruitment (flow chart, Table 1).

**Table 1 Tab1:** SPIRIT-figure of the measurement instruments and time of assessment

		Study period						
		Enrolment						
Timepoint	Type	Healthy control	1 month (SCI-T1)		2 months (Control/SCI-T2)	4 months (Control/SCI-T3)	6 months (Control/SCI-T4)	12 months (Control/SCI-T5)

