### Statistical analysis

#### Descriptive statistics

The data will be analyzed descriptively and divided into SCI and control groups. Measurement or enumeration data are presented as the mean ± SEM (standard error of the mean) or number [%] (N[%]), respectively. *T tests, chi-squared tests* or *Fisher’s exact* tests were utilized for data comparisons. **P <* 0.05 is regarded as a significant difference.

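### Controls are called matched, but the named t tests for MEP latency and CMCT neither use nor adjust for any matching

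*Protocol article*

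**What the plan says.** The label appears twice. The abstract's Methods paragraph says: "The matched healthy controls will be measured during the same period of time after recruitment". The section on recruitment and sample selection repeats it: "The matched healthy controls will be measured during the same period after recruitment". Neither place gives a matching factor, a ratio, or the kind of matching (individual or frequency).

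The control criteria, under Inclusion and exclusion criteria, read: "The inclusion criteria for healthy controls were as follows: (a) 18–75 years old, right-hand dominant (Edinburgh Handedness Inventory); and (b) stable MEPs". On exclusions: "Exclusion criteria included the above situations in which TMS could not be performed". The age range and handedness requirement are the same as for the patients.

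The analysis statements that bear on the comparison of patients with controls are these:

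- MEP latency and CMCT: "central motor conduction time (CMCT) are analyzed with independent samples" t tests.
- MEP amplitude: "The MEP amplitudes of patients and controls will be analyzed by nonparametric tests". The test is not named, and paired or unpaired is left open.
- Hemispheric conversion degree: a GEE over the five points of disease course, with no matched set mentioned.
- General comparisons under Descriptive statistics: t, chi-squared or Fisher's exact "tests were utilized for data comparisons", with no paired form named.

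Table 1 shows that age, gender, height, weight and education are collected at enrolment in both groups.

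**The concern.** Matching is a design feature that an analysis should respect. If controls are chosen to resemble patients on factors that influence latency or conduction time, the two groups' values are positively related through those factors. The difference between group means then varies less than an independent-samples formula assumes. The test keeps its error rate below the nominal level, but its intervals are too wide and the precision that the matching was meant to buy is lost.

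If no matching is done, the problem is different. Two groups each drawn from ages 18 to 75 can differ in age and gender, the t test does not adjust for either, and a reader told that the controls are matched would assume a comparability that the stated recruitment criteria do not create.

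**Working it through.** **Step 1: how the plan treats the two groups in its own arithmetic.** Inputs from Sample size calculation: P1 = 0.70, P2 = 0.26, two-sided α = 0.05, power 90%. Formula for two independent proportions with pooled variance and no continuity correction:

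n = [z₀.₉₇₅ √(2 p̄ q̄) + z₀.₉₀ √(P1Q1 + P2Q2)]² / (P1 − P2)²

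With p̄ = (0.70 + 0.26)/2 = 0.48:

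- 1.960 × √(2 × 0.48 × 0.52) = 1.960 × √0.4992 = 1.385
- 1.282 × √(0.21 + 0.1924) = 1.282 × √0.4024 = 0.813
- n = (1.385 + 0.813)² / 0.44² = 4.83 / 0.1936 = 24.9, so 25 per group

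This reproduces the stated 25 per group; power at 25 is 90.1%. The sample size, like the t tests, treats the groups as independent.

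**Step 2: size of the effect if matching is individual, 1:1.** Let ρ be the within-pair correlation of the measure. The document gives no value, so ρ from 0 to 0.5 is an assumption.

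- Variance of the mean difference assumed by the independent-samples test: 2σ²/n
- True variance under pairing: 2σ²(1 − ρ)/n
- Ratio of the assumed to the true standard error: 1/√(1 − ρ)

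The last column is the actual type I error of the nominal 5% independent-samples t test, simulated on normal pairs (100,000 runs, at 25 and at 30 pairs).

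| Assumed ρ | 1/√(1 − ρ) | Standard error too large by | Actual type I error, 25 / 30 pairs |
|---|---|---|---|
| 0 | 1.000 | 0% | 4.9% / 5.1% |
| 0.1 | 1.054 | 5% | 3.9% / 4.0% |
| 0.2 | 1.118 | 12% | 2.9% / 3.0% |
| 0.3 | 1.195 | 20% | 2.1% / 2.0% |
| 0.5 | 1.414 | 41% | 0.7% / 0.7% |

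The error is conservative throughout and vanishes at ρ = 0.

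**Step 3: frequency matching.** Balancing the groups on factors related to the measure removes those factors' contribution to the difference between means. The unadjusted test still leaves that contribution in its residual variance, so the direction is the same. The size depends on how much variance the factors explain, which the document does not give. The pair-based figures in Step 2 should not be read across to this case.

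**Step 4: does matching undermine the sample size?** A McNemar calculation (unconditional normal approximation) with the same margins and α, at 90% power, needs:

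| Assumed ρ | Pairs |
|---|---|
| 0 | 28 |
| 0.1 | 26 |
| 0.2 | 24 |
| 0.3 | 22 |

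At ρ = 0.5 the joint probabilities are impossible with these margins (one cell would be −0.02). The range of 22 to 28 straddles the stated 25 and stays below the 30 per group to be recruited.

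**Step 5: which measures the named test reaches.** Under Outcome measures, the spTMS comparison of patients with controls is set on MEP amplitude and RMT. Latency is recorded there, and CMCT is not mentioned. The explicit independent-samples wording covers latency and CMCT only.

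**The case against.** The strongest reply is that matching may mean frequency matching. The document never speaks of pairs or of a control chosen for each patient, and two-sample tests after frequency matching are common practice. The article also condenses a fuller protocol, so silence on the matching factors does not show that there are none. Both points stand in part. Frequency matching is a plausible reading, and nobody should infer from the criteria list that no matching will take place. But the article goes beyond silence: it names the test for latency and CMCT, and that test makes no use of either kind of matching.

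A reader might draw three stronger conclusions that the documents do not support:

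- **That all primary TMS comparisons are affected.** The amplitude test is unspecified and could be paired, and the conversion degree uses a GEE. The statistical section names no separate test for the ppTMS measures.
- **That the standard error is known to be 12% to 41% too large.** Those figures need 1:1 pairs and a correlation of 0.2 to 0.5. At 0.1 the figure is 5%, and at 0 there is no distortion.
- **That false positives rise or the study is the wrong size.** Under positive correlation the test is conservative, and the planned number is little changed.

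**Conclusion.** The point holds for MEP latency and CMCT. The controls are labelled matched, the stated criteria only limit eligibility, and the prescribed t tests neither use nor adjust for matching. Under individual or frequency matching on factors related to these measures, the standard errors are too large and power is lost. The size cannot be fixed from the document; under assumed 1:1 pairing it runs from 0% at ρ = 0 to 41% at ρ = 0.5. Without matching, the label is unsupported and age and gender imbalance goes unadjusted. In either case the text needs a change, but no stated figure is wrong and the target of 25 per group stands.

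**What to change.** In the section on MEP and hemispheric excitability conversion degree, replace the independent-samples t tests for latency and CMCT by a regression of the measure on group, with the matching variables as covariates. Age and gender are natural candidates because Table 1 already collects them. If matching is individual, use a pair effect instead, entered as a random effect so that a participant whose partner drops out is kept.

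Under Inclusion and exclusion criteria, state whether matching is individual or by frequency, and on which variables. If no matching is done, delete the word from the abstract and from the recruitment section; the regression with age and gender is still worth having.

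The cost is slight. Two covariates take the residual degrees of freedom at 30 per group from 2 × 30 − 2 = 58 to 56. A pure paired analysis of 30 complete pairs would have 30 − 1 = 29, which moves the two-sided 5% critical value from about 2.00 to 2.05, so pairing loses a little if the correlation is close to zero. No new data are needed, only a little more analysis work and the wording changes.

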#### Correlation analysis and multiple linear regression analysis

Correlation analysis of hemispheric excitability conversion degree and overall functional recovery was performed to determine the effects of disease course, AIS grade, and neurological level of injury. Pearson correlations between different phases/groups were calculated after the normality test. **P* < 0.05 is regarded as a significant difference.

Univariate and multivariate linear regression analyses will be conducted to validate the influence of hemispheric excitability conversion degree as an independent factor. The MBI and SCIM are set as the linear regression analysis outcomes. The inclusion criterion for univariate analysis was *P* < 0.10. **P* < 0.05 is regarded as a significant difference.

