Moreover, evaluating and predicting overall functional recovery (including motor function and ADL ability) after SCI is another target of this research. As discussed above, a recent study revealed that the M1 hand area of individuals with SCI encodes the activity information of both the UE and LE, and the movement coding of the UE and LE are highly correlated [9]. Similarly, Freund P et al. reported an increase in task-related activation in the paralyzed left M1 leg area during a right handgrip task in individuals with SCI, indicating structural associations between hand motor function and the M1 leg area [33]. In this view, the above studies support the opinion that M1 hand area and extremity motor function (including the UE and LE) are highly correlated. Therefore, changes in the hemispheric excitability of the M1 hand area may be used to assess extremity motor function and ADL ability, which could serve as potential indicators of overall functional recovery. Herein, we utilized the MS, the SCIM12 and the MAS for motor function evaluation and the MBI and SCIM for ADL ability assessment. The MS focuses on basic motor function. In addition, the total MS consists of the UEMS and LEMS, which is more convenient for distinguishing between the UE and LE. The SCIM12 evaluates the mobility of individuals with SCI indoors [25]. The MAS measures muscle tone. For ADL ability, the MBI is the most widely used scale and has been utilized to evaluate functional outcomes after SCI rehabilitation [34]. The SCIM focuses on individuals with SCI and has a relatively high sensitivity [35]. We utilize these two ADL assessment scales for mutual verification.

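### The link between hemispheric conversion and recovery is tested many times at P < 0.05 with no lead test, although the study is meant to confirm it

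*Protocol article*

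**What the plan says.** The Abstract defines the functional side of the association as a set of measures: "Overall functional status included total motor score, modified Ashworth scale score, ASIA Impairment Scale grade, spinal cord independence measure and modified Barthel index". The scale descriptions and the Discussion add sub-scores: UEMS and LEMS within the motor score, and SCIM item 12.

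*Correlation analysis and multiple linear regression analysis* sets out the association tests: "Correlation analysis of hemispheric excitability conversion degree and overall functional recovery was performed to determine the effects of disease course, AIS grade, and neurological level". It continues: "Pearson correlations between different phases/groups were calculated after the normality test", with P "< 0.05 is regarded as a significant difference". The preceding section, *MEP and hemispheric excitability conversion degree*, gives the phases, comparing the conversion degree ln(DH/NDH) "with respect to disease course (1 m, 2 m, 4 m, 6 m, and 12 m").

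A regression step follows, meant to validate conversion degree as an independent factor: "The MBI and SCIM are set as the linear regression analysis outcomes". Variables enter on a univariate P < 0.10. No visit is named, and neither outcome leads.

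The Objective includes the correlation with motor recovery. The last paragraph of the Introduction says the cohort was designed to confirm the relationship seen in the earlier cross-sectional study. *Sample size calculation* rests on a difference in proportions between SCI and control participants, not on a correlation.

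**The concern.** A study that sets out to confirm an association needs a stated test whose result decides the matter. Here the conversion degree is set against several scales, at several visits and in several groups, with the same 0.05 threshold each time. Nothing says which result settles the question. Following the rule as written, an author could report a significant correlation from one scale, visit or group as confirmation, and the error rate of that claim would not be 5%.

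The article hopes to use conversion degree as an early indicator of recovery and to inform rTMS design. A false association could therefore be carried into later work. The point concerns only the association analyses, not the between-group comparisons of the TMS primary outcomes.

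**Working it through.** **The plan's own figure.** The article gives no error rate for the correlations; its only design figure is 25 per group. With P1 = 0.70, P2 = 0.26, mean 0.48, two-sided 0.05 and 90% power:

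n = [1.960·√(2·0.48·0.52) + 1.282·√(0.70·0.30 + 0.26·0.74)]² / 0.44² = (1.385 + 0.813)² / 0.1936 ≈ 25.

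This reproduces the stated figure. It serves the group comparison and singles out no association test.

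**Inputs from the article.**
- Scales: five are listed in the Abstract. The check uses two (MBI, SCIM) or four (motor score, MAS, SCIM, MBI). AIS grade is left out because it is also a grouping factor.
- Visits: 1, 2, 4, 6 and 12 months.
- Threshold: P < 0.05 per correlation.
- SCI patients: 25, or 30 after the 20% increase (24 if 20% of 30 are lost).

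**Assumptions, not in the article.**
- AIS and injury level are each split in two, as the Discussion describes for the earlier study (AIS A / non-A, cervical / noncervical), here in equal halves.
- Inter-scale correlation is 0.5 to 0.85.
- Within-patient correlation between visits is 0.5 for conversion degree and 0.8 for the scales.
- Data are normal, and scales are oriented so that higher is better.

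**Upper guide.** For k independent tests, the chance of at least one P < 0.05 is 1 − 0.95^k. The tests here are correlated, so the chance was also simulated with no association, n = 25 and a Pearson test in each cell. Simulation error is about one to two percentage points.

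| Family | k | 1 − 0.95^k | Simulated, either sign | Simulated, predicted sign |
|---|---|---|---|---|
| MBI and SCIM, five visits, all SCI patients | 2×5 = 10 | 0.40 | 29–36% | 15–18% |
| Four scales, five visits, plus four subgroups at 12 months | 4×(5+4) = 36 | 0.84 | 55–70% | 30–38% |
| Four scales, all patients and four subgroups at every visit | 4×5×5 = 100 | 0.99 | 84–94% | 51–67% |

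The low end of each range belongs to inter-scale correlation 0.85 and the high end to 0.5.

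**Benchmark.** One two-sided test at 0.05 gives 5% for either sign and 2.5% for the predicted sign. The smallest family is therefore about six times nominal on both counts (29/5 = 5.8; 15/2.5 = 6).

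**Sensitivity.** With 24 or 30 patients, and visit-to-visit correlation of 0.3–0.9 (conversion) and 0.8–0.95 (scales), the smallest family gives 17–37% for either sign. The low end is still 17/5 = 3.4 times nominal.

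**What one test can detect.** By Fisher's z at 80% power, r = tanh[(1.960 + 0.842)/√(n − 3)]. This is about 0.55 with 24 patients and 0.49 with 30.

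**The case against.** **Direction.** The hypothesis has a sign: the Introduction says that the closer conversion is to that of healthy controls, the better the function. A significant correlation of the wrong sign contradicts the claim. This stands. A reader might infer that a supporting correlation is more likely than not, or almost certain, in a null study. The predicted-sign column does not support that in general: it passes one half only when subgroups are crossed with every visit, and the article does not say that they are.

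**Narrowing.** The regression cuts the outcomes to MBI and SCIM, so it is too strong to say that the plan lets any cell decide. This stands in part: two outcomes remain over five visits, with no lead outcome or visit.

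**The analysis plan is not shown.** A multiplicity scheme may sit there, and its absence from an article is not itself a fault. But the article does state a rule, P < 0.05 on an open set of phase and group correlations, and the point rests on that rule.

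**Hedged claims.** The Discussion speaks of potential indicators and calls for randomized trials. That moderates the consequence but does not remove the confirmatory aim in the Introduction.

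**Two inferences to avoid.** A reader might take the Discussion's account of the earlier study as selective, but it reports the null groups (cervical, AIS non-A) beside the significant ones. A reader might also fault the sentence "We utilize these two ADL assessment scales for mutual verification" as claiming independent confirmation. It makes no such claim, and requiring both scales to agree would be conservative: both significant in the predicted direction at some visit, in all patients, occurs in about 2–5% of simulated null studies. The article does not, however, make agreement a decision rule.

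**Conclusion.** The point holds in limited form. The article attaches P < 0.05 to many association tests and names no deciding one, although the association is something the study is designed to confirm. The chance of at least one false significant correlation is well above 5% in every family examined. The main range runs from 29–36% for the smallest to 84–94% for the largest, or from 15–18% to 51–67% in the predicted direction.

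These figures depend on the assumed correlations, equal subgroup halves and normal data. They depend most on which family is run, and the article leaves that open. No single percentage should be quoted as the study's error rate. The weakness should be corrected before analysis; it does not affect the TMS group comparisons.

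**What to change.** In *Correlation analysis and multiple linear regression analysis*, name one confirmatory association test at two-sided 0.05. An example is ln(DH/NDH) against SCIM total in all SCI patients, either at one stated visit or as one coefficient over all visits from a model that accounts for repeated measures. Label every other scale, visit and subgroup correlation exploratory and report it with its estimate and 95% confidence interval. If any of these are to be called significant, apply a Holm adjustment over a stated family; with 36 tests the first step would be 0.05/36 ≈ 0.0014.

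The cost is wording only, with no new data or visits. The downside is that isolated significant cells can no longer be reported as confirmed associations. The sentence on using MBI and SCIM together can stay as it is.

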### Sample size calculation

The sample size calculation was conducted via PASS 11.0 software based on the results of the MEP in our cross-sectional study [13], which showed that approximately 27% of healthy controls had a greater M1 hand area CSE in the NDH (P2 = 0.26), and approximately 70% of individuals with SCI had a greater M1 hand area CSE in the NDH (P1 = 0.7, R1 = P1/P2). Other parameters were set as follows: a significance level of α = 0.05 (two tails), power (1–β) = 90%, and standard deviation = 1. Therefore, a sample size of 25 individuals with SCI and 25 healthy controls was used. Considering the dropout rate in the cohort study, as the number of subjects increased by 20%, a minimum of 60 participants (30 individuals with SCI and 30 healthy controls) were needed.

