Based on our previous retrospective research, a correlation analysis of hemispheric excitability conversion degree and overall functional recovery was performed to investigate the effects of neurological level of injury, disease course and AIS grade. The results showed a completely different correlation tendency in patients in the SCI subgroup. Among patients with different degrees of neurological injury, patients in the noncervical injury group had a significantly positive correlation with the degree of hemispheric CSE conversion and ability to perform ADL ability, while a nonsignificant positive correlation was found in the cervical injury group. This finding may be due to the influence of cervical injury on the UE CST pathway. In patients with AIS A, the degree of hemispheric CSE conversion was significantly positively correlated with the ability to perform ADLs, while no correlation was observed in AIS non-A patients. We further observed and confirmed changes in the cortical excitability of the M1 hand area under different influencing factors over a long period of time through a prospective cohort study.

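### Effects of injury level, AIS grade and disease course on the excitability–function association are to be judged from separate correlations, with no test of a difference between them

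*Protocol article*

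**What the plan says.** The section on correlation and regression gives the correlation analysis an inferential purpose: it "was performed to determine the effects of disease course, AIS grade, and neurological level of injury". The method follows in the next sentence: "Pearson correlations between different phases/groups were calculated after the normality test". The decision rule is that P < 0.05 "is regarded as a significant difference".

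No interaction term and no comparison of correlations is named anywhere else in the article. The GEE, under MEP and hemispheric excitability conversion degree, models the conversion degree over disease course, not its relation to function. The univariate and multivariate regressions take MBI and SCIM as outcomes and ask whether conversion degree is an independent factor; they mention no interaction.

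The Discussion reports how the group's earlier retrospective study handled the same question. The noncervical group had a significant positive correlation, "while a nonsignificant positive correlation was found in the cervical injury group". AIS A was significant, and AIS non-A showed no correlation. The authors described the subgroups as having entirely different tendencies and offered an anatomical reason for the injury-level contrast. The present cohort is presented as the prospective confirmation.

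**The concern.** The stated question is whether the association differs by injury level, AIS grade or phase. The named statistic answers another question, namely whether the association differs from zero in each group taken alone. With small groups, one P value can fall below 0.05 and the other above it when the true correlations are identical. In the injury-level example both correlations were positive, so significance status is the only contrast that the Discussion reports.

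At stake are claims about the patients in whom the excitability marker tracks function. The article intends its results to inform rTMS parameter design and early prediction of recovery, and a subgroup claim of this kind would rest on a comparison that was never made.

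**Working it through.** **1. Size of the SCI group.** Inputs from Sample size calculation: "a significance level of α = 0.05 (two tails), power (1–β) = 90%, and standard deviation = 1", with P1 = 0.70 and P2 = 0.26.

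n = [z(0.975)·√(2·p̄·q̄) + z(0.90)·√(p1q1 + p2q2)]² / (p1 − p2)², with p̄ = 0.48

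= [1.960·√0.4992 + 1.282·√0.4024]² / 0.44² = 24.9, so 25 per group.

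The plan's figure is reproduced, and 25 × 1.2 = 30 enrolled. The calculation concerns an SCI-versus-control difference in proportions. The article states no power or error rate for the correlations, so 25 to 30 SCI patients is simply what the subgroups must be cut from.

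**2. Assumptions.** The article gives no subgroup sizes and no expected correlation. I assume two independent subgroups, bivariate normal data, the same true correlation ρ in both, and a two-sided t test of r at 0.05 in each. Splits of 30 are 15/15, 10/20 and 8/22; the split of 25 is 12/13. ρ runs from 0 to 0.8.

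**3. Discordance.** Let p1 and p2 be the probabilities of significance in each subgroup (100,000 simulated samples each). Then

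P(exactly one significant) = p1(1 − p2) + p2(1 − p1).

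Example, 15/15 at ρ = 0.5: 0.498 × 0.499 + 0.501 × 0.502 = 0.50. Example, 8/22 at ρ = 0.5: 0.249 × 0.312 + 0.688 × 0.751 = 0.59.

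| True ρ (equal) | 15/15 | 12/13 | 10/20 | 8/22 |
|---|---|---|---|---|
| 0 | 9.5% | 9% | 10% | 10% |
| 0.2 | 20% | 18% | 20% | 20% |
| 0.3 | 31% | 27% | 32% | 33% |
| 0.4 | 44% | 39% | 46% | 48% |
| 0.5 | 50% | 49% | 55% | 59% |
| 0.6 | 42% | 48% | 51% | 60% |
| 0.7 | 22% | 32% | 34% | 46% |
| 0.8 | 5% | 11% | 13% | 25% |

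**4. Direct test on the same simulated data.** Fisher z = [atanh(r1) − atanh(r2)] / √(1/(n1 − 3) + 1/(n2 − 3)), rejecting when |z| > 1.96. The false-positive rate is 4.7% to 5.2% in every cell.

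**5. Power of the direct test.** For ρ = 0.6 versus 0 at 15/15: atanh(0.6) = 0.693, divided by √(2/12) = 0.408, gives 1.70; Φ(1.70 − 1.96) = 40%. At 12/12 it is 31%. For 0.7 versus 0.3 it is 28% and 22%.

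**6. Disease course.** The five visits are in the same patients, so the two-independent-group calculation does not carry over, and I give no figure for that factor.

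**The case against.** Four points on the other side have weight.

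- **The size depends on assumptions.** A reader might infer that equal correlations will look like effect modification about half the time, whatever the data. The documents do not support that. With equal splits the discordance is 2p(1 − p), which cannot exceed 50%, and ρ = 0.5 at 15/15 sits at that ceiling. Over the grid above the range is about 5% to 60%. This stands, and the figure must be given with its conditions.
- **The Discussion describes an earlier study, not this plan's decision rule.** It is tempting to say that the new cohort will be read in the same way. That is a fair inference, but the article does not state it. The Pearson sentence is also loose enough to have been meant as a comparison, and a fuller plan may specify one. What remains is that the article pairs an inferential purpose with a statistic and a threshold that do not serve it, and names nothing that does.
- **Disease course and early phase.** A reader might extend the figure to disease course, or take the article to claim that the marker works in an early phase. Neither is supported: visits are repeated measures, and the Discussion reports subgroup results only for injury level and AIS grade.
- **Importance.** The primary outcomes are the spTMS and ppTMS measures, and the overall association with MBI and SCIM is also examined by regression. Subgroup modification is secondary to both, which limits the severity.

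The low power of a direct test does not rescue the planned reading. It means that these data can support few subgroup claims.

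**Conclusion.** The concern holds in a limited form. The named analysis cannot answer the question set for it, and the earlier study's reading shows that the misinterpretation is not hypothetical. For injury level and AIS grade, assuming two independent subgroups of 8 to 22 patients with equal true correlations of 0.4 to 0.6, a significant/nonsignificant split arises in roughly 40% to 60% of cases, against about 5% for a direct test. At ρ = 0.2 it is 18% to 20%. At ρ = 0 it is still about 10%, roughly twice the error of a direct test. At ρ = 0.8 it is 5% to 25%. For disease course the logical gap is the same, but its size is not quantified here. This should be fixed before analysis; it does not threaten the primary comparison.

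**What to change.** State that effect modification will be claimed only from a direct test, one modifier at a time, for the outcomes that the plan already models (MBI and SCIM).

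- **Injury level and AIS grade:** ln(DH/NDH) × level (cervical versus noncervical) and ln(DH/NDH) × AIS (A versus non-A), or a Fisher z comparison of the two correlations at a given visit.
- **Disease course:** ln(DH/NDH) × visit in a repeated-measures model that respects clustering within participant. This can be the GEE already planned, with small-sample robust standard errors, or a mixed model with a random slope.
- **Reporting:** each interaction with its 95% CI, labelled exploratory (two outcomes by three modifiers is already six tests). Subgroup and phase correlations are shown descriptively with CIs.

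Putting all modifiers into one random-intercept model is not advised. It needs 14 fixed effects with 25 to 30 patients. In a simulation with 26 patients, five visits, a mean slope of 0.5 and no true interaction (400 replicates, all assumed), its false-positive rate for the level and AIS interactions was 5% to 6% when slopes were identical across patients. It rose to 10% to 11% with a slope SD of 0.3, and to 13% to 15% with 0.5.

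The cost is a change of analysis wording, on the same data and visits. The downside is low power (about 40% even for ρ = 0.6 versus 0 at 15/15), so fewer subgroup claims will be possible.
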